# Therapeutic efficacy of acupuncture on motor dysfunction in ischemic stroke patients with hemiplegia and its EEG characteristics: protocol for a randomized, sham-acupuncture controlled, assessor-and-statistician-blinded trial

**DOI:** 10.3389/fneur.2025.1653873

**Published:** 2025-09-26

**Keywords:** acupuncture therapy, ischemic stroke, limb dysfunction, electrophysiological mechanisms, randomized controlled trial, study protocol

## Abstract

**Background:**

Stroke is the second leading cause of death in the world, with high disability rate in survivors, among which ischemic stroke accounts for over 80% of the total. Limb dysfunction is a common neurological deficit symptom left by ischemic stroke. Timely rehabilitation therapy in the early recovery stage of stroke is important for neurological function improvement. Acupuncture therapy for “simultaneous treatment of phlegm and blood stasis,” selecting acupoints based on pathogenic characteristics of ischemic stroke, has been applied to treat stroke patients with hemiplegia in our center, and it has exhibited significant effects. However, high-quality clinical evidence of this acupuncture strategy is still lacking. Therefore, the present study aims to evaluate the efficacy and safety of acupuncture therapy in improving limb function of patients with recovery-stage ischemic stroke.

**Methods:**

This study will be a single-center, randomized, assessor-and-statistician-blinded, sham acupuncture-controlled clinical trial. After informed consent signing, 70 eligible patients with limb dysfunction in post-stroke recovery stage will be randomized into the treatment group or sham acupuncture group in a 1:1 ratio. The treatment course will last for 2 weeks, and the scale evaluation and EEG examination will be conducted before and after treatment. The primary outcome is the changes of limb function pre and post treatment using the modified Fugl-Meyer scale. Secondary outcomes include score changes in Berg Balance Scale, Fugl-Meyer Assessment Sensory Function Scale, Modified Ashworth Score, Barthel Index and TCM syndrome score pre and post treatment. Additionally, we will employ EEG to evaluate regulation effects of acupuncture on cortical neuronal excitability and functional connectivity across brain regions in stroke patients, and screen EEG-based biomarkers with predictive value.

**Discussion:**

This study aims to evaluate the efficacy and safety of acupuncture therapy in stroke patients with hemiplegia, and to explore electrophysiological mechanisms of the therapeutic effects. The study will provide high-quality clinical evidence for the application of acupuncture therapy with acupoint combination based on the TCM theory in neurological rehabilitation for ischemic stroke.

**Clinical trial registration:**

itmctr.ccebtcm.org.cn, identifier ITMCTR2025001171.

## Introduction

1

, Stroke is one of the major diseases threatening human health in the world. According to statistics, the prevalence of stroke in China had reached 26 million by 2021. Stroke is characterized by a prolonged disease course, high medical cost, and high recurrence rate, which seriously affect patients’ life quality and impose a significant economic burden on society. With the improvement of medical standards in recent years, the mortality rate of stroke has decreased (1), however, its disability rate remains as high as 70 to 80% (1, 2). Most patients suffer from varying degrees of neurological impairment, such as hemiplegia, spasticity, dysphagia, sensory dysfunction, cognitive deficits, hemianopsia, and aphasia, among which hemiplegia is the most common post-stroke sequela, significantly impacting patients’ physical and mental states. If not treated timely and effectively, it will lead to permanent disability. The occurrence of neurological deficit symptoms is tightly associated with neuronal damage, impaired vascular regeneration, disruption of interhemispheric connections and disturbance of synaptic activities in the brain (3).

Rehabilitation therapy is the primary method to restore impaired limb function in stroke patients by enhancing neuronal activities, increasing postsynaptic excitability, and promoting the regeneration of dendritic spines and the recovery of myelin sheaths (3). The conventional rehabilitation for stroke primarily includes neuromuscular electrical stimulation, physical therapy, occupational therapy, and rehabilitation robots (4). However, the high cost and cumbersome training methods make it difficult for patients to adhere to the therapy in long term, thus presenting limited effectiveness (5). In China, acupuncture experienced a long history over 2,000 years and has been widely applied in the treatment of limb dysfunction after stroke (6). Owing to its simplicity of operation, effectiveness, and safety, acupuncture may serve as an alternative for improving post-stroke sequelae with minimal adverse effects (7). Studies have suggested that acupuncture, as a form of somatosensory stimulation, can induce plastic changes among different representations in the motor cortex, modulate interhemispheric competitive inhibition, and improve cerebral cortical function (8, 9). Acupuncture applied to the unilateral limb can stimulate neuronal excitability in bilateral brain regions, increase cerebral blood flow, and enhance the consistency of neuronal activity in the motor area of the affected hemisphere (10). It has been reported that bilateral needling method of hand-foot 12 needles can improve the motor recovery post-stroke and modify cerebro-cerebellar voxel-mirrored homotopic connectivity (11). Scalp acupuncture therapy combined with exercise therapy can significantly improve stroke patients’ ability to participate in daily activities (12). However, the acupoint selection in these studies has failed to integrate with the pathogenic characteristics of stroke in TCM, thus not fully leveraging the advantages of syndrome differentiation in acupoint selection. Moreover, the mechanisms underlying the therapeutic effects of acupuncture for hemiplegia remain unclear, lacking the support of objective evidence, which limits the development and application of acupuncture in stroke rehabilitation to some extent.

According to TCM, phlegm and blood stasis are two major pathogenic products contributing to the occurrence of ischemic stroke (13). Studies indicate that the predominant TCM syndrome types for stroke are wind-phlegm obstructing collaterals syndrome and qi deficiency with blood stasis syndrome. Manifestations of blood stasis and phlegm turbidity syndromes are particularly prominent during stroke recovery (14) and positively correlate with worsening neurological deficits (15). The acupoints employed in acupuncture treatment are mainly distributed along the Twelve Regular Meridians, and they exert different therapeutic effects based on the pathways of meridians and functional characteristics of the zang-fu organs they are associated with. In TCM, it is believed that the Yangming Meridian is abundant in both qi and blood, and it nourishes the sinews and tendons. Acupuncture applied to this meridian can promote the qi flow of the Yangming Meridian, supplement qi, and tonify blood, contributing to the recovery of limb function in patients with hemiplegia (16). Additionally, TCM holds that “the spleen is the source of phlegm,” acupuncture applied to the Spleen Meridian can strengthen functions of the spleen and stomach and alleviate the pathological accumulation of phlegm-turbidity in the meridians (17). The Shaoyang Meridian, situated in the half-exterior-half-interior position of the body, functions as a pivot that regulates the flow of qi, disperses blood stasis to promote circulation, and unblocks the meridians and collaterals (18). Therefore, based on TCM meridian theory and stroke pathogenic characteristics, we formulate the therapeutic principle of “simultaneous treatment of phlegm and blood stasis” and select acupoints comprising Jianyu (LI5), Quchi (LI11), Hegu (LI4), Waiguan (SJ5), Zusanli (ST36), Fenglong (ST40), Xuehai (SP10), Sanyinjiao (SP6), and Xuanzhong (GB39) for stroke treatment. By using the specialized acupuncture method featuring acupoint combinations for phlegm and blood stasis syndromes, our center has achieved remarkable therapeutic outcomes in post-stroke patients with hemiplegia. Therefore, it is necessary to conduct a standardized, high-quality clinical trial to evaluate the efficacy of acupuncture in improving limb function in stroke patients with hemiplegia and to investigate the related mechanisms contributing to its therapeutic effects.

Electroencephalogram (EEG) is an important method for assessing brain function and widely used in clinical practice. It tracks and records the tiny electrical signals produced by cortical neuronal activity in real time by placing electrodes on the scalp. Brainwaves in different frequency bands reflect synchronized neuronal activities across distinct brain regions (19). Since EEG has a temporal resolution in milliseconds, it can capture changes in neuronal electrical activity more rapidly than MRI and is highly sensitive to abnormalities in brain metabolism and neural function (20). Due to its simplicity and non-invasive nature, EEG has been applied to evaluate the therapeutic effect after intervention for brain diseases. As evidenced by EEG, in stroke patients with better clinical outcomes, the healthy hemisphere tended to compensate for the affected side, and kinematic and EEG metrics were reported to be relevant for evaluating early post-stroke motor recovery (21). Additionally, event-related desynchronization (ERD) during action observation, reflecting reduced coordination of neural activity, was validated as an early predictor of motor recovery in subcortical stroke (22). These metrics provide important prognostic information that can be used to optimize treatment strategies. Herein, we design a randomized, assessor-and-statistician-blinded, parallel-controlled clinical trial, for assessing the efficacy and safety of acupuncture therapy, featuring acupoint combination for “simultaneous treatment of phlegm and blood stasis,” in treating limb dysfunction in ischemic stroke patients with hemiplegia. We will employ functional scales to evaluate patients’ clinical outcomes and use EEG to capture neurophysiological changes after acupuncture, including neural excitability and brain functional connectivity. Further, EEG metrics will be linked with clinical outcomes, demonstrating its multiple values in efficacy assessment, mechanism interpretation, and prognosis prediction.

## Methods and analyses

2

### Study design

2.1

This is a single-center, assessor-and-statistician-blinded, randomized, sham acupuncture-controlled clinical trial. The study aims to evaluate the efficacy and safety of acupuncture therapy, featuring acupoint combination for “simultaneous treatment of phlegm and blood stasis,” in treating ischemic stroke patients with hemiplegia. The study has been registered on itmctr.ccebtcm.org.cn (Registration No. ITMCTR2025001171). SPIRIT checklist is shown in Supplementary file 1.

The study will recruit 70 eligible ischemic stroke patients with unilateral limb dysfunction who meet the inclusion criteria. After signing informed consent, the participants will be randomized into acupuncture group or sham acupuncture group in a 1:1 ratio. All participants will receive a two-week treatment. Basic information will be collected before treatment (Day −1 to 0), and electroencephalogram (EEG) examination and scale evaluation will be conducted before (Day −1 to 0) and after the two-week treatment (Day 15). Allocation information will be confidential to assessors. The study process is shown in Figure 1 and the timeline for enrolment, intervention and assessment is shown in Table 1. The study will be started in June 2025 and complete recruitment by June 2028. The entire study is expected to be finalized by December 2028.

**Figure 1 fig1:**
[figure not shown]
Flow diagram of the study.

**Table 1 tab1:** Participant timeline.

	Enrolment and baseline	Intervention period (2 weeks, 5 times per week)				
Timepoint	Before treatment	Day 1–5	Day 6–7	Day 8–12	Day 13–14	Day 15
Patients						
Recruitment and screening	√					
Signed informed consent	√					
Randomization	√					
Allocation	√					
Interventions						
Acupuncture		√		√		
Sham acupuncture		√		√		
Outcome measures						
FMA	√					√
BBS	√					√
FMA-S	√					√
MAS	√					√
MBI	√					√
TCM symptom score	√					√
EEG	√					√
Patients’ compliance	√	√	√	√	√	√
Safety assessment						
Adverse events	√	√	√	√	√	√
ECG	√	√	√	√	√	√

FMA, short form Fugl-Meyer assessment for motor function; BBS, the Berg balance scale; FMA-S, the sensory scale of the Fugl-Meyer assessment; MAS, the modified Ashworth scale; MBI, the modified Barthel index; EEG, Electroencephalogram data collection and processing; ECG, Electrocardiogram examination.

### Patient recruitment

2.2

Patient screening and recruitment will be conducted from June 2025 to June 2028 in Traditional Chinese Medicine Comprehensive Ward of Shanghai Putuo District Central Hospital. Ischemic stroke patients with unilateral limb dysfunction who meet the inclusion criteria will be fully informed about the objective, content, benefits, and potential risks of the study, and be randomly assigned to different groups after informed consent.

### Diagnostic criteria

2.3

The diagnostic criteria for Western medicine refer to the “Chinese Guidelines for Diagnosis and Treatment of Acute Ischemic Stroke 2023” (23), while the diagnostic criteria for TCM syndrome differentiation in stroke refer to the classification criteria for phlegm syndrome and blood stasis syndrome outlined in the “Diagnostic and Efficacy Evaluation Criteria for Stroke” (24).

### Inclusion criteria

2.4

Patients who meet diagnostic criteria of Western medicine for ischemic stroke, combined with CT or MRI;Patients who meet diagnostic criteria for phlegm and blood stasis obstructing meridians in TCM syndrome;Aged between 30 and 80, inclusive;First occurrence, or those with a previous stroke but without sequelae;1 week to 3 months after the onset of stroke;Lesion in one cerebral hemisphere with unilateral hemiplegia, Brunnstrom stage II-IV;Right handedness;Patients with clear minds, clinically stable conditions, and limb dysfunction caused by stroke.

### Exclusion criteria

2.5

Patients who suffered from transient ischemic attack, hemorrhagic stroke, and asymptomatic cerebral embolism;Patients with severe multi-system diseases and mental disorder;Patients with severe consciousness disorders, cognition impairment, and post-stroke depression;Excluding factors that interfere with EEG signals (such as receiving transcranial magnetic stimulation within 1 month) (25);Patients with severe head skin injuries;Patients with severe needle phobia or allergic to acupuncture needles.

### Dropout criteria

2.6

Patients who fail to cooperate during treatment, voluntarily request to withdraw from the trial, or discontinue participation;Patients who experience unbearable pain during acupuncture and are unable to continue treatment;Patients who develop severe complications during treatment and are no longer suitable for further treatment.

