### Sample size calculation

2.7

Sample size for this study is estimated according to the formula for the comparison of means in a randomized controlled trial. Referring to the relevant literatures (26, 27), we estimate the pooled standard deviation (*σ*) of the treatment group and the control group to be 7.81, and the difference between the means of the two groups (*δ*) to be 6.59. We set the significant level (*α*) at 0.05, the Type II error rate (*β*) at 0.1, and the statistical power (1-β) at 0.9. After substituting the values into the formula, calculated sample size per group requires 30 cases. Considering a 15% dropout rate, a total of 70 cases will be enrolled.

$$n=\frac{2{\left(z_{\alpha }+z_{\beta }\right)}^{2}*\sigma^{2}}{\delta^{2}}$$

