### Safety assessment

2.13

Safety will be assessed by observing and recording adverse events and conducting electrocardiogram (ECG) examination. Common adverse events associated with acupuncture therapy include bleeding, needle fainting, subcutaneous hematoma, and pain. The acupuncturist responsible for treatment needs to evaluate the severity of adverse events and promptly record and report the occurrence time, symptoms, duration, severity, treatment measures taken, and resolution time of such events. The grading for the severity of adverse events is categorized into three levels: grade 1 for mild, grade 2 for moderate, and grade 3 for severe or medically significance. Patients experiencing severe adverse events should stop acupuncture therapy, receive timely care, and the events must be reported to the Ethics Committee of Shanghai Putuo District Central Hospital within 24 h.

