### Statistical analysis

2.16

All data will be analyzed using SPSS 27.0 statistical software. In accordance with the intention-to-treat (ITT) principle, patients who have received at least one treatment session will be included in the analysis. Basic information, baseline data, and efficacy evaluation will be analyzed using both the full analysis set (FAS) and per-protocol set (PPS). In case of inconsistent results between the two datasets, further analysis and evaluation will be conducted. Missing data will be imputed using multiple imputation method. For continuous outcomes, post-treatment data are presented as mean±SD if normally distributed with equal variances; otherwise, they are presented as median (IQR). ANCOVA will be used to adjust for baseline values and confounders (e.g., age, gender, revascularization therapy status), with adjusted mean differences and 95% CIs reported. For categorical data, frequencies and percentages will be presented, and potential confounders will be screened via univariate analysis before constructing stepwise logistic regression models to adjust for confounders and report odds ratios with 95% CIs, followed by validation of the model’s goodness of fit. Further, patients will be grouped based on infarction location to analyze EEG indicators in each subgroup. Receiver operating characteristic (ROC) curve analysis will be conducted to evaluate the predictive value of EEG as an efficacy indicator for acupuncture response, with the area under the curve (AUC) and 95% CI reported. For correlation analysis, Pearson correlation will be applied to normally distributed continuous data, while Spearman correlation will be used for ordinal data. All data analysis will be conducted using two-tailed tests with a significant level of 5%.

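### Section 2.6 lists patients who only stop needling as dropouts with those who leave the trial, so their Day 15 FMA may never be taken

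*Protocol article*

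**What the plan says.** Section 2.6 (Dropout criteria) has three items. The first covers patients who do not cooperate during treatment, who ask to withdraw from the trial, or who end their participation. The other two describe the end of treatment only: "Patients who experience unbearable pain during acupuncture and are unable to continue treatment" and "Patients who develop severe complications during treatment and are no longer suitable for further treatment". All three carry the same label, and the section does not say what follows from it.

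Section 2.1 schedules the scales before treatment "and after the two-week treatment (Day 15"). Table 1 shows no FMA between these two times, and the Discussion confirms that no later follow-up is planned.

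Section 2.16 states the intention-to-treat principle, under which "patients who have received at least one treatment session will be included in the analysis". It analyses both a full analysis set and a per-protocol set, and adds that "Missing data will be imputed using multiple imputation method".

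**The concern.** A patient who cannot bear the needling, or who is no longer fit for it, has not thereby refused a motor assessment. That patient can usually still be scored at Day 15. Calling the patient a dropout invites site staff to close the case at that point. There is one FMA after baseline, so a missed score cannot be replaced from another visit.

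Keeping such patients in the full analysis set does not restore the score. With no intermediate FMA, imputation would rest on baseline data and on patients who completed the course. It would assume that stoppers did as well as similar completers in their own arm, which is doubtful when the reason for stopping is pain or a complication.

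The loss may also be uneven. Section 2.10.2 and Table 2 specify insertion to 1 or 1.5 cun with manipulation for 1 minute. Section 2.10.3 specifies a sham that is superficial or non-penetrating and is not manipulated. If more acupuncture patients stop and they do worse than completers, the imputed analysis favours acupuncture. A later analysis plan can choose the imputation model, but it cannot recover scores that were never taken.

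**Working it through.** **Inputs from the protocol (Sections 2.7 and 2.16).** SD 7.81; difference 6.59; two-sided alpha 0.05; power 0.90; 70 patients, 1:1, so 35 per arm; dropout allowance 15%.

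**The plan's own figure.** n = 2 × (1.960 + 1.282)² × 7.81² / 6.59² = 29.5, so 30 per arm, as stated. An allowance of 30 × 1.15 = 34.5 rounds to 35 per arm, 70 in total. Dividing by 0.85 instead gives 36 per arm, 72 in total. The size of the trial is not in question here.

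**Inputs that are assumed.** The documents give no stopping rates and no outcome for stoppers. Let p be the share of the acupuncture arm that stops and is unscored, and r the share of the 6.59-point effect that stoppers keep. Imputation is taken to be missing-at-random with arm in the model.

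**Step 1: stopping in the acupuncture arm only.** Imputation gives stoppers the full effect when they truly have r of it, so the overstatement is p × (1 − r) × 6.59.

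| p (patients of 35) | r = 0 | r = 0.5 |
|---|---|---|
| 5% (about 2) | 0.33 | 0.16 |
| 10% (about 4) | 0.66 | 0.33 |
| 15% (about 5) | 0.99 | 0.49 |

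Per patient who gains nothing, this is 6.59 / 35 = 0.19 points.

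**Step 2: stopping in both arms.** Suppose stoppers in each arm fall 6.59 points short of completers in their own arm. The bias is (pA − pS) × 6.59, where pA and pS are the acupuncture and sham rates:
- 10% v 5%: +0.33
- equal rates: 0
- 5% v 10%: −0.33

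**Step 3: scale.** The unadjusted standard error of the difference with all 70 scored is 7.81 × √(2/35) = 1.87. The Step 1 figures with r = 0 are 0.33/1.87 = 0.18, 0.66/1.87 = 0.35 and 0.99/1.87 = 0.53 standard errors. With r = 0.5 they are about half of that.

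**Step 4: check by simulation.** There were 4000 trials of 35 per arm, analysed by ANCOVA with an assumed baseline correlation of 0.5 and five imputations with arm in the model. Stoppers gained nothing in the first three rows.

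| Stoppers | Mean estimate, all scored | Mean estimate, stoppers imputed |
|---|---|---|
| 2 acupuncture | 6.19 | 6.57 |
| 4 acupuncture | 5.88 | 6.62 |
| 5 acupuncture | 5.65 | 6.61 |
| 4 acupuncture, half the effect kept | 6.19 | 6.57 |
| 4 v 2, both 6.59 short | 6.18 | 6.57 |
| 4 v 4, both 6.59 short | 6.58 | 6.61 |

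The gaps agree with the closed formula, allowing for simulation error and for whole patients (4 of 35 is 11.4%, not 10%).

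**The case against.** The strongest objection is that the harm is not in the text. Section 2.6 is a bare list and attaches no consequence to being a dropout. Several other places point towards continued contact:
- Section 2.1 and Table 1 schedule Day 15 with no exception for patients who stopped.
- Section 2.10.1 gives everyone two weeks of rehabilitation apart from the needling.
- Section 2.13 asks for the resolution time of adverse events.
- Section 2.15 follows patients during the course.
- Section 2.16 invokes intention to treat.

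A full protocol, not shown, may settle the matter. This stands in part: the loss is inferred, and assessing stoppers may already be the intention. But none of these places says that a patient who stops is scored at Day 15, while the label in 2.6 suggests the reverse. That label is a stated rule of trial conduct, not a detail left to an analysis plan.

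The objection also rightly limits several stronger readings that a reader might infer:
- **That 2.13 contradicts 2.6.** It does not. "Patients experiencing severe adverse events should stop acupuncture therapy" is an instruction about needling. It can stand beside a list that names patients unfit for further treatment.
- **That 2.7 counts dropouts as unscored.** It says only "Considering a 15% dropout rate, a total of 70 cases will be enrolled". This is a routine allowance and does not say who the dropouts are or whether they are assessed.
- **That every patient on the list could be scored.** Non-cooperating patients share an item with those who leave the trial and may not be assessable. The point is confined to pain and complications.
- **That the planned comparison of analysis sets ("In case of inconsistent results between the two datasets, further analysis and evaluation will be conducted") is defeated.** The article does not define the per-protocol set, so how closely the two sets would agree is unknown.

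The objection is also right that the exclusion of severe needle phobia, the rubber pad in both groups and the trained acupuncturists should keep stopping rare.

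**Conclusion.** The point holds as a minor one. Section 2.6 does not separate stopping treatment from leaving the trial, and on the ordinary reading it gives up an obtainable primary outcome that the analysis cannot restore.

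The size rests wholly on assumed stopping rates, assumed outcomes of stoppers and missing-at-random imputation with arm. On those terms a few tenths of a point is likely. The 0.99 extreme needs 15% of the acupuncture arm, as large a share as the whole dropout allowance, to stop and gain nothing. The direction is not fixed: the bias is zero when rates and shortfall are equal in both arms, and negative if sham patients stop more often.

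A reader might infer that the trial's conclusion is in danger. The figures do not support that, because a true 6.59-point effect would survive every case shown. Confidence is medium, since the loss of scores is inferred from one word.

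**What to change.** Keep the rules for stopping needling, but set them apart in 2.6 from withdrawal from the trial. Add: 'Patients who stop treatment remain in the trial and have the Day 15 FMA and other scales unless they withdraw consent to assessment; these scores are used in the full analysis set.' Leave the one-session rule, the per-protocol set and multiple imputation in 2.16 as they are, with imputation only for scores still missing. The trial is already recruiting, so the change is worth making soon.

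The cost is a short amendment and a few assessments at a visit already scheduled: about 2 to 5 patients at 5% to 15% stopping in one arm, or about 10 of 70 at 15% in both (70 × 0.15 = 10.5). Some patients will take effort to reach and some will refuse.

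The estimated effect may be slightly smaller, because stoppers count at their true value. The sample size does not change. With all 70 scored, power from the noncentral t distribution at 5%, 10% and 15% acupuncture-arm stopping is 0.91, 0.88 and 0.84 if stoppers gain nothing. It is 0.92, 0.91 and 0.90 if they keep half the effect. The plan's 30 completers per arm at 6.59 points give 0.89 by the same method.
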